## Abstract

**Background:**

Partial hepatectomy remains a primary therapeutic intervention for various hepatic diseases. However, several intraoperative factors, including surgical manipulation, substantial blood loss, the need for blood transfusions, and hypoxic stress, can significantly impair liver function. Current perioperative strategies aimed at protecting the liver exhibit certain limitations. Transcutaneous auricular vagus nerve stimulation (taVNS), an emerging non-invasive neuromodulation technique, has demonstrated potential in preserving organ function through vagus nerve-mediated anti-inflammatory mechanisms. This study is designed to evaluate the hepatoprotective effects of taVNS on liver function in patients undergoing elective partial hepatectomy under general anesthesia.

**Methods/design:**

In this single-center, prospective, double-blind, randomized controlled trial, 140 patients scheduled for partial hepatectomy will be randomly allocated in a 1:1 ratio to either the transcutaneous auricular active-taVNS or sham taVNS groups. Both groups will receive 60-min stimulation sessions at four predefined time points: (1) at the onset of the first hepatic portal occlusion, (2) post-extubation, (3) on postoperative day 1 (6:00–7:00 a.m.), and (4) on postoperative day 2 (6:00–7:00 a.m.). The primary outcome is alanine aminotransferase (ALT) level measured in venous blood samples collected at 7:00 a.m. on postoperative day 2. Secondary outcomes include postoperative levels of inflammatory markers, renal function indicators, quality of recovery, gastrointestinal function recovery, pain, fatigue, anxiety, incidence of postoperative delirium, and time to first flatus, bowel movement, and oral intake, all of which will be assessed using validated instruments.

**Discussion:**

Postoperative liver function dysfunction following partial hepatectomy remains a significant clinical complication that negatively impacts patient prognosis and long-term survival outcomes. TaVNS, an emerging non-invasive neuromodulation technique, has demonstrated considerable potential for perioperative organ protection in preclinical studies. This study aims to provide robust evidence regarding the therapeutic efficacy of taVNS in reducing hepatic injury after partial hepatectomy. By introducing a novel approach to perioperative hepatic protection, taVNS may contribute valuable insights into the development of multimodal hepatoprotective strategies.

## Introduction

1

Liver cancer ranks as the sixth most prevalent malignant tumor worldwide globally and is the third leading cause of cancer-related mortality (1). Epidemiological projections anticipate a 55% global increase in incidence, with 81% of new cases and 80% of related deaths concentrated in Asia and Africa. China, which bears one of the highest liver cancer burdens worldwide, faces substantial challenges in the prevention and management of the disease (2). Among liver tumors, benign hepatic hemangiomas are typically asymptomatic; however, when these tumors reach a significant size, they may cause compressive symptoms and potentially lead to severe complications, such as tumor rupture and life-threatening hemorrhage (3). Clinical studies with long-term follow-up of 236 patients diagnosed with hepatic hemangiomas demonstrated that 61% exhibited tumor growth, indicating a statistically significant progression rate (4). Progressively enlargement of hepatic hemangiomas is now considered an indication for surgical intervention (3). In patients presenting with localized hepatocellular carcinoma or hepatic hemangioma, partial hepatectomy allows for complete tumor resection while preserving adequate liver volume, thereby contributing to improved patient prognosis (5–7). However, several perioperative factors—including manipulation of the liver parenchyma during surgery, intermittent occlusion of the portal vein leading to hepatic ischemia–reperfusion injury (HIRI), intraoperative massive blood loss and transfusion, and chronic perioperative stress—can trigger and aggravate hepatic dysfunction, potentially leading to postoperative liver failure and increased mortality (5, 8, 9). A meta-analysis of 32 studies involving 19,503 patients reported considerable variability in post-hepatectomy complication rates. Specifically, minor hepatectomies were associated with hepatic dysfunction and severe complication rates ranging from 7.2 to 21.6%, whereas major hepatectomy showed an overall severe complication rate of 38.8%. In-hospital mortality was reported at 5.9%, with 30-day and 90-day mortality rates of 4.6 and 6.1%, respectively. Patients with compromised residual liver function and insufficient liver volume exhibit significantly rates of higher morbidity and mortality (10). A subsequent meta-analysis of 37 studies encompassing a total of 14,096 patients confirmed a significant association between postoperative severe hepatic dysfunction, liver failure, and decreased overall survival as well as disease-free survival (11). Therefore, the implementation of effective perioperative hepatoprotective strategies is of critical importance. In contemporary clinical practice, anesthesia preconditioning (APC) and ischemic preconditioning (IPC) are recognized as potential hepatoprotective interventions (12, 13). However, due to ongoing controversies regarding the clinical efficacy of IPC, its routine use remains limited. Notably, dexmedetomidine-based APC has shown potential in preserving hepatic function following partial hepatectomy, however, further validation through large-scale, multicenter clinical trial is necessary to confirm its long-term efficacy (12, 14, 15).

Preclinical studies suggest that vagus nerve stimulation (VNS) activates anti-inflammatory pathways, thereby exerting hepatoprotective effects (16–18). Research has shown that glutathione is a key antioxidant enzyme in the liver, the synthesis of which relies on the enzymatic activities of glutathione s-transferase (GST) and glutamate–cysteine ligase (GCL), formerly known as glutathione synthase (GSS). Evidence indicates that VNS enhances glutathione metabolism by modulating the GSS-GSH-GST axis, leading to a significant increase in the mRNA and protein expression of levels GSS and GST. As a result, VNS effectively elevates hepatic glutathione levels, enhances the liver’s intrinsic antioxidant capacity, and attenuates perioperative inflammatory responses (19). VNS activates the cholinergic anti-inflammatory pathway through the release of acetylcholine from vagus nerve efferent fiber terminals. Acetylcholine binds to *α*-7 nicotinic acetylcholine receptors (*α*-7nAChR) expressed on macrophages and Kupffer cells, thereby inhibiting their activation and reducing the production of pro-inflammatory cytokines such as interleukin-6 (IL-6) and tumor necrosis factor-*α* (TNF-α). This ultimately suppresses hepatic inflammation and alleviates liver injury. Notably, Kupffer cells also express α-7nAChR, exhibiting functional characteristics similar to those observed in macrophages (20, 21). Furthermore, studies suggest that stimulation of the hepatic branch of the vagus nerve following partial hepatectomy enhances hepatocyte proliferation by promoting the binding of acetylcholine to M3 receptors expressed on liver progenitor cells, thereby activating these cells and augmenting their proliferative and regenerative potential (22). Accumulating evidence suggests that the nuclear factor erythroid 2-related factor 2/heme oxygenase-1 (Nrf2/HO-1) signaling pathway confers protective effects on the liver. In a mouse model of hepatic ischemia–reperfusion, VNS at a frequency of 20 Hz induces the release of acetylcholine from vagal nerve terminals, which subsequently activates *α*-7nAChR and initiates the activation of the Nrf2/HO-1 pathway, leading to a significant reduction in hepatic inflammatory responses and ischemia–reperfusion injury (23).

Transcutaneous auricular vagus nerve stimulation (taVNS) is an innovative, cost-effective, and non-invasive neuromodulation technique. Research has demonstrated that taVNS achieves therapeutic outcomes comparable to those of traditional VNS across a range of clinical applications, including epilepsy, depression, chronic insomnia, and cerebral-cardiovascular protection. Given its favorable safety profile and ease of implementation, taVNS is increasingly recognized as a promising alternative therapeutic approach (24). In the field of clinical research, taVNS has demonstrated considerable promise in cerebrocardiovascular protection. Accumulating evidence indicates that taVNS administered during acute middle cerebral artery occlusion can reduce infarct volume and improve stroke outcomes through multiple mechanisms, including activation of the cholinergic anti-inflammatory pathway, suppression of excitotoxicity, and preservation of blood–brain barrier integrity (25, 26). Furthermore, a clinical study revealed that low-frequency taVNS (20 Hz) applied as a preconditioning intervention in patients with myocardial infarction, and continued for 2 h post-reperfusion, significantly reduced biomarkers of myocardial injury and levels of inflammatory cytokines (27, 28). The therapeutic potential of taVNS in protecting vital organs such as the heart and brain has been increasingly investigated. However, to date, no clinical studies have evaluated the impact of taVNS on hepatic injury.

Based on existing research, we propose the hypothesis that taVNS may offer hepatoprotective benefits during the perioperative period of partial hepatectomy. This study is designed to assess the efficacy of taVNS in preserving liver function in patients undergoing partial hepatectomy, with the objective of establishing a more robust theoretical basis for its clinical application and exploring a novel multimodal approach to perioperative liver protection.

## Methods and analysis

2

### Study design

2.1

This is a single-center, prospective, double-blind, randomized controlled clinical trial that will be conducted at the Affiliated Hospital of Xuzhou Medical University. A total of 140 patients scheduled for elective partial hepatectomy will be enrolled. The study protocol has received ethical approval from the Ethics Committee of the Affiliated Hospital of Xuzhou Medical University (approval number: XYFY2024-KL521-01) and has been registered with the Chinese Clinical Trial Registry (http://www.chictr.org.cn, Registration number: ChiCTR2400092005). Recruitment of participants is currently in progress, following strict adherence to predefined inclusion and exclusion criteria. Written informed consent will be obtained from all participants prior to enrollment. The study follows the Standard Protocol Items: Recommendations for Interventional Trials (SPIRIT) guidelines (Supplementary material 1) (29). The flow of patient recruitment, intervention, and outcome measurement is summarized in Figure 1.

**Figure 1 fig1:**
[figure not shown]
Flow diagram of the study.

### Eligibility criteria

2.2

Patients eligible for partial hepatectomy will be recruited from the Affiliated Hospital of Xuzhou Medical University according to predefined inclusion and exclusion criteria, which will be assessed by the research team the day before surgery. All participants will provide written informed consent prior to undergoing baseline evaluation (Supplementary material 2).

### Inclusion criteria

2.3

Age: 18–75 yearsScheduled for elective partial hepatectomy (liver cancer, hepatic hemangiomas)American Society of Anesthesiologists (ASA) grade I-IIIAble to comprehend study protocol and assessment scalesCapable of effective communication with researchers

### Exclusion criteria

2.4

Refusal to provide informed consent.Patients with neurological or psychiatric disorders that impede experimental cooperation, such as refractory epilepsy, Parkinson’s disease, and treatment-resistant depressionAbnormal ear anatomySevere cardiovascular and cerebrovascular disease (myocardial infarction within 12 months, NYHA heart rating ≥2, PaO2 < 60 mmHg)History of pacemaker implantation.Instrument allergy (including ear dermatitis)Severe hepatic impairment (e.g., fulminant hepatitis resulting in Child-Pugh Class C) and renal dysfunction (e.g., serum creatinine >442 μmol/L, glomerular filtration rate <45 mL/min/1.73 m^²^). We supplemented the definitions of severe liver and kidney function disorders to further enhance the comprehensiveness of our research.Previous partial hepatectomyBiliary tract disease (calculi, infection, obstruction)

### Dropout criteria

2.5

Voluntary withdrawalProtocol violationConcomitant medication interfering with trial outcomesLoss to follow-upPostoperative intensive care unit admission

Participants have the right to withdraw from the study at any time and for any reason without experiencing medical discrimination or disruption to their standard clinical care. The research team will ensure that all participants continue to receive appropriate medical care and will thoroughly document the reasons for withdrawal. Moreover, researchers may discontinue a participant’s involvement in the study if severe organ dysfunction, non-compliance with study protocols, or the occurrence of serious adverse events (SAEs) is observed.

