### Randomization and blinding

2.6

Participants will randomly be allocated to active-taVNS treatment or sham taVNS groups at a 1:1 ratio, based on a computer-generated random number sequence. The allocation process is strictly confidential and managed by administrative personnel uninvolved in study design and implementation. Each participant will be assigned a unique, de-identified alphanumeric code, encompassing the research center code, enrollment order, and randomization group identifier, ensuring data traceability. A designated research coordinator will maintain sealed, sequentially numbered opaque envelopes containing randomization assignments. Immediately before entering the operating room, a blinded circulating nurse will open the envelope to determine group assignment. Following verification of the group allocation details, the envelopes will be resealed, and this procedure will be conducted without disclosing the information to the patients. To ensure blinding, we will informed patients during preoperative consultation about potential sensory experiences during treatment, including sensations of pricking, needle-like stimulation, warmth, and vibration. We will explicitly emphasize that individual perception of stimuli varies significantly and that sensation intensity should not be used to assess treatment efficacy. Moreover, all stimulation devices will be designed with uniform appearance, with differences limited to electrical output parameters, thereby further preserving the integrity of the blinding procedure. The device will be preset to patient-specific maximum tolerable parameters by independent researchers not involved in the research, and will remain in a black screen state upon entering the operating room. All individuals involved in outcome assessment, data analysis, surgical procedures, and study participants remained blinded to group allocation. With regard to the initial administration of stimulation during hepatic portal occlusion, standard practice at this institution involves the surgeon informing the anesthesiologist and circulating nurse about surgical progress at this stage. However, these personnel were not provided with details regarding the specific stimulation protocol, thereby ensuring the maintenance of blinding within the surgical team throughout the procedure. Prior to study commencement, outcome assessors will accept rigorous blinding training, familiarizing themselves with assessment procedures and standards to minimize subjective influences on results.

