#### Primary outcome

2.10.1

The primary endpoint is serum alanine aminotransferase (ALT) levels on postoperative day 2. Perioperative hepatic injury occurs in two distinct phases. The first phase, occurring 2–6 h after reperfusion, is characterized by Kupffer cell-induced oxidative stress and the initiation of cell necrosis and apoptosis. The second phase, spanning 6–48 h after reperfusion, involves inflammatory cell aggregation in the hepatic microvascular system, including sinusoids and post-sinusoidal regions, accompanied by sinusoidal congestion, neutrophil adhesion leading to blood flow obstruction, and inflammatory cell extravasation into the hepatic parenchyma (31, 32). Furthermore, evidence indicates that intermittent stimulation effectively alleviates patient discomfort and improves treatment safety (33). Based on these pathological mechanisms, we implemented taVNS intervention throughout the entire hepatic injury inflammatory response to maximize inflammation mitigation and minimize hepatic damage. Liver injury severity is classified as follows: ① Mild acute liver injury (ALI) is typically defined as 2 × upper limit of normal (ULN) ≤ ALT < 5 ULN; ② Moderate ALI is typically defined as 5 ULN ≤ ALT < 15 ULN; ③ Severe ALI requires: International Normalized Ratio (INR) ≥ 2.0, ALT ≥ 10 ULN, serum total bilirubin (TBiL) ≥ 3.0 mg/dL, and absence of hepatic encephalopathy (34–36). Baseline venous blood samples will be obtained during the preoperative anesthesia visit after obtaining informed consent (t0). The primary endpoint will be venous blood samples collected at 7:00 AM on the second postoperative day (t4) after stimulation cessation.

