### Sample size

2.13

Sample size was calculated using PASS 15.0 software. The primary outcome measure was ALT level on postoperative day 2. Preliminary data showed a mean ALT level of 249.8 ± 147.9 U/L after partial hepatectomy. In a pre-experimental phase, taVNS interventions reduced ALT to 174.9 ± 103.5 U/L (approximately 30% reduction). With a significance level (*α*) of 0.05 and statistical power (1 − *β*) of 90%, a two-sided test determined a minimum sample size of 63 participants per group. Accounting for a 10% potential dropout rate, we plan to recruit 140 patients and randomly allocate them to active-taVNS and sham taVNS groups. Regarding the validation of the Minimal Clinically Important Difference (MCID), we estimated the MCID using a stepwise approach based on previous research methods (44). In this experiment, the sham taVNS group’s mean ALT ± standard deviation on postoperative day 2 was 249.8 ± 147.9 U/L, while the active-taVNS group was 174.9 ± 103.5 U/L, with a pooled standard deviation of 127.64. Conventionally, the MCID range is typically set between 0.2 and 0.5 times the pooled standard deviation, resulting in a reasonable MCID interval of 25.53 to 63.82. The mean difference between groups (*Δ*) was 74.9. When the intergroup difference exceeds the upper limit of the MCID, it indicates that the observed effect difference has clinical significance, thus supporting the reasonableness of the MCID determination.

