### Statistical analysis

2.14

Statistical analyses will be performed using SPSS software (version 27.0; IBM) and statistical charts will be generated with GraphPad Prism (version 8.0). Normality of data will be assessed using the Kolmogorov–Smirnov test, and variance homogeneity will be evaluated by the Levene test. Normally distributed continuous data will be presented as mean ± standard deviation, while non-normally distributed data will be reported as median with interquartile range.

Statistical analyses will employ independent samples t-tests for normally distributed continuous data and Mann–Whitney U tests for non-normally distributed data. Time-to-event outcomes will be evaluated using Kaplan–Meier curves and Log-rank tests. Multivariate analyses will utilize multiple linear or logistic regression models based on dependent variable type. Repeated measures data will be analyzed using generalized estimating equations. The analysis will follow the intention-to-treat principle, with multiple imputation addressing missing data the per-protocol Analysis will be included as part of the sensitivity analysis. A significance level of *α* = 0.05 will be applied, with *p* < 0.05 considered statistically significant.

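### The dropout rules do not separate stopping stimulation from leaving the study, so day-2 ALT may be missing in the most injured patients and unequally by arm

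*Protocol article*

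**What the plan says.** Section 2.5 (Dropout criteria) gives a flat list: "Voluntary withdrawalProtocol violationConcomitant medication interfering with trial outcomesLoss to follow-upPostoperative intensive care unit admission". It then adds a discretionary rule: "researchers may discontinue a participant’s involvement in the study if severe organ dysfunction, non-compliance with study protocols, or the occurrence of serious adverse events (SAEs)". The object of that second rule is involvement in the study, not the stimulation.

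Section 2.6 places allocation before surgery: "Immediately before entering the operating room, a blinded circulating nurse will open the envelope to determine group assignment". Section 2.10.1 fixes the primary endpoint: "The primary endpoint will be venous blood samples collected at 7:00 AM on the second postoperative day (t4) after stimulation cessation".

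Section 2.14 states: "The analysis will follow the intention-to-treat principle, with multiple imputation addressing missing data the per-protocol Analysis will be included as part of the sensitivity analysis". Section 2.13 raises 63 per group to 140 in total for 10% dropout. Section 2.11 follows adverse events until they resolve or stabilise, and Table 1 schedules them to day 30.

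**The concern.** Postoperative ICU admission can only happen after randomisation, and the other listed events can also fall between randomisation and the day-2 sample. ICU admission, severe organ dysfunction and serious adverse events are plausible consequences of a bad hepatic course. The Introduction itself links blood loss, transfusion and ischaemia–reperfusion to hepatic dysfunction and liver failure, and section 2.10.1 grades liver injury partly by ALT.

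If a patient who meets one of these criteria is treated as out of the study, the ALT most likely to be lost is a high one. The loss need not be equal by arm:

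- If stimulation protects the liver, sham loses more of its worst values and the effect is understated.
- If stimulation leads to more ICU stays or serious adverse events, the active arm loses its worst values and looks better than it is.

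The net direction would not be known in advance. Delirium and recovery outcomes to day 30 are exposed in the same way.

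**Working it through.** **1. The plan's own figures.** The difference is 249.8 − 174.9 = 74.9 U/L. The pooled SD is √[(147.9² + 103.5²)/2] = 127.645. The normal approximation gives n = 2(1.960 + 1.2816)² × 127.645²/74.9² = 61.03, so 62 per arm. The noncentral t gives 63, as stated. Then 63/0.90 = 70 per arm, 140 in total. The sample size reproduces, and it counts dropouts as contributing no endpoint.

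**2. Timing.** The envelope is opened just before theatre (2.6) and the endpoint is drawn at 7:00 a.m. on day 2 (2.10.1). Events in that window can remove the primary value. Events after day 2 cannot.

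**3. Illustration of size.** The document gives no removal rates, so these are assumptions: log-normal ALT with the section 2.13 means and SDs; a fraction q of an arm removed by a latent risk with correlation ρ to log ALT; no imputation.

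- σ = √ln(1 + (SD/mean)²). Sham: √ln(1 + (147.9/249.8)²) = 0.548. Active: also 0.548.
- Mean ALT among those kept = mean × Φ(z − ρσ)/(1 − q), with z = Φ⁻¹(1 − q).

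Example at ρ = 0.8, so ρσ = 0.4386 for sham (0.4384 for active):

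- Sham, q = 0.10: 249.8 × Φ(1.2816 − 0.4386)/0.90 = 249.8 × 0.8004/0.90 = 222.2.
- Active, q = 0.05: 174.9 × Φ(1.6449 − 0.4384)/0.95 = 174.9 × 0.8862/0.95 = 163.2.
- Difference 59.0 U/L, against 74.9 planned.

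| ρ | True difference 74.9; 10% sham and 5% active removed | No true effect (both arms 249.8 ± 147.9); 5% sham and 10% active removed |
|---|---|---|
| 0.2 | 71.5 | 2.5 |
| 0.3 | 69.6 | 3.8 |
| 0.5 | 65.6 | 6.5 |
| 0.8 | 59.0 | 10.9 |
| 1.0 | 54.3 | 13.8 |

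The second column is the observed difference in U/L. The third is the false benefit in U/L.

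**4. What imputation can recover.** Section 2.12 records blood loss, occlusion frequency and duration, and extent of resection. An imputation model using them can recover the part of the loss that they explain. The part that depends on the unseen ALT itself, given those covariates, stays. The table imputes nothing, so it does not estimate the bias of the planned analysis.

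**The case against.** The case on the other side is substantial, and several stronger readings that a reader might infer do not hold.

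- *The day-2 ALT is certain to go uncollected.* The document nowhere cancels the sample. Loss is inferred from ended involvement, from the silence on later sampling, and from the dropout allowance. Section 2.11 also says that independent monitoring will be arranged to collect research data when adverse events occur, though it does not name the ALT sample.
- *All these patients must be removed.* For severe organ dysfunction, non-compliance and serious adverse events the wording is permissive. Only the list before it is flat.
- *Safety data are lost.* They are not: section 2.11 and Table 1 keep adverse-event follow-up going. ALT, delirium and recovery scores have no such assurance.
- *Section 2.14 is contradicted outright.* Dropout criteria followed by imputation can be made coherent. The fair statement is that removing patients for protocol violation or interfering medication sits poorly with intention-to-treat.
- *Interfering medication means liver-protective drugs given for high ALT.* The text does not define the term, so this cannot be assumed.
- *Severe complication rates of up to 38.8% after major hepatectomy show how many would be removed.* That figure is not a rate of removal before day 2.

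On size, power barely moves, because trimming high values also shrinks the SD. At 10%/5% removal from 70 per arm it is about 90% at ρ = 0.5 and 92% at ρ = 0.8. The false benefit stays below 25.53 U/L, the protocol's lower bound for a clinically important difference. Type I error in the null case is about 6% to 8% at ρ = 0.5 to 0.8.

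All of this limits how strongly the point may be put. It does not remove it. A condensed article may leave detail to the full protocol, but the dropout rule is stated here, and an analysis plan cannot recover blood that was not drawn.

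**Conclusion.** The point holds. Section 2.5 ties leaving the study to post-randomisation events, some of them plausibly related to the primary endpoint, and does not secure the day-2 ALT afterwards. Intention-to-treat with multiple imputation under missing at random is only a partial remedy.

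The size is uncertain. In the complete-case illustration, the planned 74.9 U/L is understated as about 54 to 71 U/L, or a false benefit of about 2.5 to 14 U/L arises where there is no effect. Both ranges rest on assumed removal rates of 5% and 10%, log-normal ALT and correlations from 0.2 to 1.0. The main threat is bias of unknown direction, not lost power. Section 2.1 says that recruitment is in progress, and a missed day-2 sample cannot be recovered, so the change should be made now.

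**What to change.** Rewrite section 2.5 so that stopping stimulation and leaving the study are separate.

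- Record ICU admission, protocol violation, non-compliance, interfering medication, severe organ dysfunction and serious adverse events as intercurrent events, with any missed sessions. None of them should end data collection.
- Draw the t4 and t6 samples and do all feasible follow-up in every randomised patient, unless consent for follow-up is withdrawn or the patient is truly lost.
- Analyse as randomised, and use these events only to define the per-protocol sensitivity set.
- Include blood loss, occlusion frequency and duration, and extent of resection in the imputation model.
- Add a delta-adjusted missing-not-at-random sensitivity analysis for any ALT still missing.

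No view is taken on when stimulation should be stopped.

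The cost is a wording amendment and blood draws that may have to be taken on the ICU. Expect a somewhat wider ALT spread and some questionnaires that cannot be completed. No larger sample is needed: at the planned SD, the normal approximation gives about 93% power with all 70 per arm observed, against about 91% with 63.
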